## **6. Sample size calculation**

The number of samples for the home-based program required in this study is based on a dichotomous variable, which is the primary endpoint, to secure enough patients for a stable and sufficient power. The primary endpoint of this study is the unplanned hospitalization within six months following enrollment. This study aims to determine the differences in the effects by comparing the odds ratio based on the proportion of unplanned hospitalizations in the intervention and control groups. Although no previous intervention study with a similar design has been conducted outside of Korea, the difference in pre- and post-intervention changes between the intervention and control groups should be approximately 20% (20% less in the intervention group) based on the literature review. The number of institutions in both groups is three. The parameters will be estimated using a generalized estimation equation (GEE) to compensate for the cluster effects of the study participants. The comparisons between the two groups will be analyzed using a logistic regression model, which is used to compare the effects of dichotomous outcome variables while considering other confounding variables. Therefore, a power of 80%, a significance level of 0.05 to control for type 1 error, and a 20% difference in the number of unplanned hospitalizations by intervention was used to calculate the sample size. For a ratio of 1:1 for participants in each group, the minimal sample size should be 396 patients

in total, including 198 patients for three clusters in the intervention groups and 198 patients for three clusters in the control group (assuming within-cluster coefficient=0.015).

Within-cluster coefficient (Intraclass correlation coefficient, ICC) was estimated using the analysis of variance (ANOVA) estimation method according to similar previous studies. The calculation formula is as follows (Sheng et al., 2012; Chen et al., 2015)

In the formula, 
$$n_A = \frac{1}{k-1}(N - \sum n_i^2/N) \quad MSB = \frac{1}{k-1}(\sum Z_i^2/n_i - (\sum Z_i)^2/N)$$

$$MSW = \frac{1}{N-k}(\sum Z_i - \sum Z_i^2/n_i)$$
  $k$  is the number of cluster and  $N$  is the total number of study participants.  $n_i$  and  $Z_i$  are the number of participants in group  $i$  and number of patients with endpoints in group  $i$ , respectively. Incidence rates by group were extracted from a study by Chen et al. (2015) and applied in the present study.

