| k | N   | $n_1, n_2$ | $Z_1, Z_2$ | $n_A$ | MSB     | MSW      | ICC      |
|---|-----|------------|------------|-------|---------|----------|----------|
| 6 | 396 | 198,198    | 40,20      | 39.6  | 0.20202 | 0.127946 | >0.01441 |

| Power   | Sample size | # of cluster | Allocation | Average Cluster size | Effect size | ICC   | Alpha |
|---------|-------------|--------------|------------|----------------------|-------------|-------|-------|
| 0.72584 | 264         | 4            | ri(1)      | 66                   | 0.2         | 0.01  | 0.05  |
| 0.66263 | 264         | 4            | ri(1)      | 66                   | 0.2         | 0.015 | 0.05  |
| 0.5826  | 264         | 4            | ri(1)      | 66                   | 0.2         | 0.02  | 0.05  |
| 0.72584 | 264         | 4            | ri(1)      | 66                   | 0.2         | 0.01  | 0.05  |
| 0.83007 | 396         | 6            | ri(1)      | 66                   | 0.2         | 0.015 | 0.05  |
| 0.75675 | 396         | 6            | ri(1)      | 66                   | 0.2         | 0.02  | 0.05  |
| 0.88014 | 396         | 6            | ri(1)      | 66                   | 0.2         | 0.01  | 0.05  |
| 0.83007 | 396         | 6            | ri(1)      | 66                   | 0.2         | 0.015 | 0.05  |
| 0.8658  | 528         | 8            | ri(1)      | 66                   | 0.2         | 0.02  | 0.05  |
| 0.95162 | 528         | 8            | ri(1)      | 66                   | 0.2         | 0.01  | 0.05  |
| 0.92004 | 528         | 8            | ri(1)      | 66                   | 0.2         | 0.015 | 0.05  |
| 0.92905 | 660         | 10           | ri(1)      | 66                   | 0.2         | 0.02  | 0.05  |

ICC: Intraclass correlation coefficient

ri(1): The ratio of allocation for the intervention and control groups = 1:1

- Assuming a maximum dropout rate of 15% in each institution, the final number of enrolled study participants should be 57 for each institution, totaling 342 participants. The expected minimum power is 78.8% (PASS 2022, v22.0.2)
- Three institutions will participate in the intervention group (Seoul National University Hospital, Chung-Ang University Hospital, and Dongguk University Ilsan Hospital) and control group (Kyunghee University Hospital, Bundang CHA Hospital, and Bundang Seoul University Hospital). With a total of 396 expected participants, there will be sufficient power to test the differences in the effects.

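### Section 6 sizes the trial on two incompatible pairs of event rates: 20.2% v 10.1% in the ICC worksheet, and an unstated 20-point gap (50% v 30%, or 70% v 50%) in the power table

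*Protocol*

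**What the plan says.** Protocol Section 6 sizes the trial on the binary primary endpoint, unplanned hospitalization within six months. The arms are compared by odds ratio in a GEE logistic model. The expected effect "should be approximately 20% (20% less in the intervention group) based on the literature review", and "a 20% difference in the number of unplanned hospitalizations by intervention was used to calculate the sample size". The other inputs are 80% power, "a significance level of 0.05 to control for type 1 error", 1:1 allocation, three hospitals per arm and an ICC of 0.015.

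The section then derives the ICC by an ANOVA estimator, with Z defined as the count of patients who have the endpoint in each group. On the inputs it says "Incidence rates by group were extracted from a study" (a cited pilot cohort of home-based palliative care in older adults) and that they were applied here. The worksheet row reads "6 | 396 | 198,198 | 40,20 | 39.6 | 0.20202 | 0.127946 | >0.01441": 40 and 20 events among 198 and 198 patients.

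The power table that follows has effect size 0.2 in every row and no control or intervention rate. The row relied on is "0.83007 | 396 | 6 | ri(1) | 66 | 0.2 | 0.015 | 0.05". The section adds a minimum power of 78.8% with 342 patients and concludes: "With a total of 396 expected participants, there will be sufficient power to test the differences in the effects". The synopsis repeats the 80% target and the 78.8%.

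**The concern.** Power for a binary endpoint depends on both event rates, not only on their difference. The one pair that can be read from Section 6 has a gap of 10.1 points. The power table needs a gap of 20 points, which cannot be taken from a control rate of 20.2% without all but abolishing the event. The worksheet supplies the ICC and the table supplies the power, so the stated power draws on one pair of rates for its ICC and on another pair for its effect.

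At stake are the figures on which the trial was justified: 80% as the target, 83% in the table, 78.8% as the minimum, and the closing claim of sufficient power. A reader cannot tell which hospitalization rate the trial was planned for, and the answer moves power from about 80% to about 50%.

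**Working it through.** **Inputs from Section 6.** N = 396 in six clusters of m = 66, or N = 342 with m = 57; ICC 0.015; alpha 0.05 (sidedness not stated; two-sided reproduces the table); worksheet counts 40/198 = 20.2% and 20/198 = 10.1%.

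**Worksheet.** With the usual ANOVA estimator, ICC = (MSB − MSW)/[MSB + (n_A − 1)MSW] = (0.20202 − 0.127946)/(0.20202 + 38.6 × 0.127946) = 0.01441, as printed. The 40 and 20 are therefore the counts actually used.

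**Power table.** Take a Wald test of the log odds ratio, the scale that Section 6 names:

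- n_eff = (N/2)/[1 + (m − 1)ICC] per arm
- b = |ln OR|, SE = √{[1/(p₁q₁) + 1/(p₂q₂)]/n_eff}
- power = Φ(b/SE − 1.96)

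The table gives no rates, so I searched pairs 20 points apart. At 50% v 30%, b = ln[(0.5/0.5)/(0.3/0.7)] = 0.8473 and 1/(p₁q₁) + 1/(p₂q₂) = 4 + 4.7619 = 8.7619. Results for the 396- and 342-patient cases:

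| N | ICC used | n_eff | Power | Printed |
|---|---|---|---|---|
| 396 | 0.01 | 120.0 | 0.88014 | 0.88014 |
| 396 | 0.02 | 86.09 | 0.75675 | 0.75675 |
| 396 | 0.015 | 100.25 | 0.81756 | 0.83007 |
| 396 | 0.014 | 103.66 | 0.83007 | 0.83007 |
| 342 | 0.015 | 92.93 | 0.788 | 78.8% |

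The 264-, 528- and 660-patient rows at ICC 0.01 and 0.02 also match to every printed decimal. The 264- and 528-patient rows labelled 0.015 match only at 0.014 (0.66263 and 0.92004; at 0.015 they would be 0.64809 and 0.91141). So the 83% rests on an ICC of 0.014 and the 78.8% on 0.015.

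The mirror pair 70% v 50% gives identical values. Other 20-point pairs do not: for N = 396 and ICC 0.01, 40% v 20% gives 0.915 and 60% v 40% gives 0.868, against 0.880 printed. Other readings of 0.2 miss the 83% by far: a 20% relative reduction gives about 11% power from a 20% control rate and about 30% from 50%, and a standardised difference of 0.2 gives 29%.

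**Incompatibility.** 20.2% − 20 points = 0.2%.

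**Power at the worksheet rates, ICC 0.015.** b = ln[(40/158)/(20/178)] = 0.8123, and 1/(p₁q₁) + 1/(p₂q₂) = 6.203 + 11.012 = 17.216.

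- N = 396: design effect 1 + 65 × 0.015 = 1.975; n_eff = 100.25; SE = √(17.216/100.25) = 0.4144; b/SE = 1.960; power 50.0%.
- N = 342: design effect 1 + 56 × 0.015 = 1.84; n_eff = 92.93; SE = 0.4304; b/SE = 1.887; power 47.1%.
- Pooled two-proportion test as a cross-check: 51.4% and 48.4%.

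The odds ratios are close (e^−0.8123 = 0.44 against e^−0.8473 = 0.43). Power falls because the rarer event roughly doubles the variance term, from 8.76 to 17.22.

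**The case against.** The best reply is that 40 and 20 serve only to obtain an ICC. They appear in the worksheet row and nowhere else, the sentence about their source closes the ICC paragraph, and the 20% effect is introduced separately on the strength of a literature review. On that reading the power table is coherent with its own effect size and merely omits its control rate. Much of this stands. A reader might infer that the trial simply has 51% power rather than 83%, or that the table is miscalculated. The documents support neither as a flat statement: the table follows exactly from 50% v 30%, apart from the mislabelled ICC rows.

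The reply does not remove the conflict. The text does not confine the rates to the ICC. It says they were applied to this study, counts them as patients with the endpoint, and scales them to this trial's own 198 per arm. The rates that do support the power claim are nowhere written.

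Two further inferences should be resisted:

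- That 198 per arm came from a calculation at 20.2% v 10.1% without clustering. The apparent fit depends on the method (80.3% by the pooled test, 78.7% on the log odds ratio), and 198 is simply 3 × 66.
- That putting 50% v 30% through the worksheet shows power of about half either way. The worksheet's two groups are the trial arms, so this would only feed the treatment gap back in as an ICC.

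**Conclusion.** The point holds as an inconsistency within Section 6, with a conditional consequence. The worksheet pair and the power-table pair cannot both be the expected rates. If the worksheet rates are the expected ones, power is about 50–51% at 396 patients and 47–48% at 342, and the statements of 83%, 78.8% and sufficient power fail. If a control rate near 50% (or 70%) was intended, the power figures stand, except that the 396-patient row at ICC 0.015 should read 81.8%; the protocol must then state that rate and its source.

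These figures assume a two-sided 0.05 test, ICC 0.015, equal clusters and a normal approximation. A t reference with 4 degrees of freedom, as six clusters would suggest, would lower power further, to about 34% at the worksheet rates with 396 patients. That 0.2 is an absolute gap, and that the pair is 50% v 30% or its mirror, is inferred from the exact match and not stated. Which event and time window the cohort's rates describe cannot be checked from the protocol.

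**What to change.** State one control rate and one HBMC rate for the six-month primary endpoint, with a source, and base the power statement on that pair. Then:

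- If 20.2% and 10.1% stand, restate power as about 50% (396) and 47% (342) on the log-odds-ratio scale, and delete the claim of sufficient power.
- If a control rate near 50% is intended, write it with its source, say that the worksheet rates are not the expected rates for this trial, and correct the rows labelled ICC 0.015 (81.8% for 396 patients).

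In either case say that 0.2 is an absolute difference, and bring the synopsis into line. The cost is a rewrite of Section 6 and the synopsis sizing text, and the first option makes the stated power less favourable. No additional patients or hospitals are proposed.

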|                               | 
unscheduled hospitalization within 6 months of enrollment in the study. The study aims to reveal the difference in the effectiveness of the HBMC program by examining the odds ratio based on the proportion of unscheduled hospitalizations in the intervention and control groups. Although no previous study using an intervention with a similar design has been conducted overseas, the difference between the intervention and control groups can be expected to be approximately 20% (20% lower in the HBMC group) based on the literature review. The number of institutions in each group will be 3. The parameters will be estimated using generalized estimating equations (GEE) to consider the cluster effect of the participants at each institution. The two groups will be compared using a logistic regression model, a model of comparison of the dichotomous outcome variable. Considering the above analysis method and the assumptions of the power of 80%, a significance level of 0.05 to control type I error, a 20% change in the number of unscheduled hospitalizations before and after the intervention (20% lower in the HBMC group), and 1:1 ratio of participants between the intervention and control groups, the minimum sample size should be 198 in the intervention group and 198 in the control group, totaling 396 participants (assuming within-cluster coefficient of 0.015). Assuming a maximum dropout rate of 15%, the final number of participants to be recruited is approximately 57 for each cluster, and a total of 342 participants are expected to be recruited. The expected minimum power is 78.8% (PASS 2022, v.22.0.2).
 
- Three institutions (i.e., Seoul National University Hospital, Chung-Ang University Hospital, and Dongguk University Ilsan Hospital) will participate as the intervention institutions, and three institutions (i.e., Kyung Hee University Hospital, Cha University Bundang Medical Center, and Seoul National University Bundang Hospital) will participate as the control institutions.
 |

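### The ICC worksheet enters the two arms as clusters with k = 6, so the 0.015 has no between-hospital basis; the power rows labelled 0.015 were evidently run at 0.014

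*Protocol*

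**What the plan says.** Protocol section 6 (Sample size calculation) says the "Within-cluster coefficient (Intraclass correlation coefficient, ICC) was estimated using the analysis of variance (ANOVA) estimation method according to similar previous studies". It prints formulas for n_A, MSB and MSW in which k "is the number of cluster and" N the total number of participants, while n_i and Z_i "are the number of participants in group" i and the number with the endpoint in that group. On the data source it says "Incidence rates by group were extracted from a study by" one cited cohort of home-based palliative care.

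The worksheet below the formulas sets k = 6 and N = 396, but lists only n = 198, 198 and Z = 40, 20. It gives n_A = 39.6 and, for MSB, MSW and ICC, "0.20202 | 0.127946 | >0.01441".

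The sample size of 396 (three hospitals and 198 patients per arm) is then justified "assuming within-cluster coefficient=0.015"; the Overview says the same, "assuming within-cluster coefficient of 0.015". The power table has rows labelled ICC 0.01, 0.015 and 0.02. The row for 396 patients at 0.015 shows 0.83007. A bullet below it gives 78.8% for 57 patients per hospital after 15% dropout, and the section ends by stating that 396 participants give sufficient power.

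**The concern.** An ICC for this design has to measure how far hospitals in the same arm differ in their rate of unplanned hospitalization. The ANOVA estimator needs one count per hospital for that. The worksheet has one count per arm, and 198 + 198 already uses up all 396 patients. The only difference between groups that it can see is the one between intervention and control, which is the effect the trial is meant to detect.

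With three hospitals per arm, power depends strongly on the ICC. A reader who sees a formula, a data source and a numerical result will take 0.015 as supported by evidence. If it is not, the claim of sufficient power rests on an unsupported figure. In addition, if the rows labelled 0.015 were run at another value, the table and the dropout bullet beneath it are not on the same footing.

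**Working it through.** **1. Reproducing the worksheet.** Inputs from section 6: k = 6, N = 396, n = 198 and 198, Z = 40 and 20 (20.2% and 10.1%). The last step is not printed; I used the standard ANOVA estimator, ICC = (MSB - MSW) / (MSB + (n_A - 1) × MSW).

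- n_A = (396 - (198² + 198²)/396) / 5 = (396 - 198)/5 = 39.6
- MSB = (1600/198 + 400/198 - 3600/396) / 5 = (10.1010 - 9.0909)/5 = 0.20202
- MSW = (60 - 10.1010) / 390 = 0.127946
- ICC = 0.074074 / (0.20202 + 38.6 × 0.127946) = 0.014409

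All four match the printed values, so this is how the figure was made. The n_A of 39.6, which should be a typical cluster size, fits neither six hospitals (66) nor two groups (198).

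**2. What the result measures.** Changing one input at a time:

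| Input | ICC |
|---|---|
| Arms equal (30, 30), k = 6 | -0.026 |
| 40, 30 events, k = 6 | -0.017 |
| 40, 20 events, k = 6 (as printed) | 0.0144 |
| 40, 10 events, k = 6 | 0.077 |
| 40, 20 events, k = 2 to match two groups | 0.034 |
| Six hospitals of 66, same rate within each arm | 0.0087 |

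With equal arms MSB is 0 and the result is -1/38.6 = -0.026 whatever the event rate. With k = 2, n_A = 198, MSB = 1.0101 and MSW = 60 - 10.1010 over 394 = 0.12665. With six equal hospitals, MSB and MSW are exactly the printed ones and only n_A changes, to 66. The estimate within one arm is then -1/65 = -0.0154, because no variation between hospitals was entered. The value follows the assumed benefit throughout.

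**3. Reproducing the power table.** The protocol gives an effect of 0.2 but no arm rates, and does not state sidedness. Assumptions: two-sided 0.05, a Wald test of the log odds ratio, and 50% v 30% (70% v 50% gives identical results by symmetry).

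- (ln OR)² = (ln(0.3/0.7))² = 0.71791
- W = 1/(0.5 × 0.5) + 1/(0.3 × 0.7) = 8.7619
- Power = Φ( √[ n × 0.71791 / (8.7619 × (1 + (m - 1) × ICC)) ] - 1.960 ), with n per arm and m per hospital

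For 396 patients at ICC 0.01: √[198 × 0.71791 / (8.7619 × 1.65)] = 3.13565, power 0.88014, as printed. All distinct rows labelled 0.01 or 0.02 reproduce. The rows labelled 0.015 do not:

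| Patients | Printed | At 0.015 | At 0.014 |
|---|---|---|---|
| 264 | 0.66263 | 0.64809 | 0.66263 |
| 396 | 0.83007 | 0.81756 | 0.83007 |
| 528 | 0.92004 | 0.91141 | 0.92004 |

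This does not depend on the exact rates. Write W/(ln OR)² as a variance on the 0.2 scale: 0.04 × 8.7619/0.71791 = 0.48819. Every row labelled 0.01 or 0.02 implies 0.48818 to 0.48819. The 0.015 rows imply 0.47212 to 0.47213 at their label, and an ICC of 0.01400 if 0.48819 is kept.

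**4. Dropout figure.** With 57 per hospital, n = 171 and the design effect is 1 + 56 × 0.015 = 1.84; power is 0.7880, as stated. At 0.014 it would be 0.8002.

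**5. Sensitivity, 396 patients, same formula.** ICC 0.01 / 0.015 / 0.02 / 0.03 / 0.05 gives 88.0 / 81.8 / 75.7 / 65.0 / 49.8%. The last two ICC values are my assumptions.

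**The case against.** The strongest reply is that 0.015 is worded as an assumption in both the Overview and section 6, and that the table already shows 0.01 to 0.02, including 0.75675 at 0.02 for 396 patients. That stands in part: the plan does disclose a nearby ICC at which power is below 80%. But section 6 also says the value was estimated and prints the estimate, and that claim is wrong.

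A reader might go further and put 0.034 into the power formula, or the value the worksheet would return at more widely separated rates, and conclude that the trial is badly underpowered. The document does not support that. Those values come from the same faulty worksheet and are treatment effects too. The equally artificial 0.0087 would give about 90% power by the same route, so choosing only the unfavourable variants would be selective. The hospital ICC may be 0.015, lower or higher.

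Nor should one infer that every power figure at 0.015 is inflated. The 78.8%, which is the lowest power the text quotes, was run at 0.015. The mislabelled row for 396 patients moves by only 1.3 points and stays above 80%. That it was run at 0.014 is inferred from the numerical pattern; the protocol does not say so.

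**Conclusion.** The ICC derivation is invalid and should not stand. It carries no information on variation between hospitals, so 0.015 is an unsupported assumption and the true ICC is unknown in either direction. This conclusion needs only the printed inputs and the standard final step of the estimator, which returns the printed result.

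The labelling error is minor: printed power is too high by 1.5, 1.3 and 0.9 points for 264, 396 and 528 patients. It rests on a five-decimal match in all three distinct rows, with arm rates that are inferred.

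The consequence for design is that the statement of sufficient power holds only conditionally. With 396 patients, power is about 82% at an ICC of 0.015 and already about 76% at 0.02. Correcting the derivation does not in itself show that power is lower than planned.

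**What to change.** In section 6:

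1. Delete the ICC formulas and worksheet. State 0.015 as a plain assumption, or replace it with an estimate from hospital-level event rates within one arm or under usual care.
2. Correct the rows labelled 0.015 to 0.648 (264 patients), 0.818 (396) and 0.911 (528), and print the arm rates and test behind the table.
3. Keep the 0.01 to 0.02 range and add higher assumed values. For 396 patients, ICC 0.01 / 0.015 / 0.02 / 0.03 / 0.05 gives about 88 / 82 / 76 / 65 / 50% at the inferred rates.
4. Qualify the closing statement on sufficient power by saying that it depends on the ICC and falls below 80% by 0.02. Leave the 78.8% dropout figure as it is.

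The cost is one paragraph and one table. No extra patients are required.

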| Participants                                                   | Advanced solid cancer patients with mobility difficulties undergoing cancer treatment and their family caregivers                                                                                                                                                                                                                                                                                                                                                                                                                                                                                                                                                                                                                                                                                                                                                                                                                                                                                                                                                                           |
| Number of Study Participants (based on the number of patients) | 
 
- Total number of participants (6 institutions): 396; Participants at the intervention institution: 66
 
- Three institutions will be assigned to the intervention and control groups each. A total of 396 patients will be enrolled. The ratio of participants between the intervention and control groups will be 1:1 with 198 patients enrolled in each group.
 
- The rationale for sample size calculation: The number of samples in the home care management program in this study is based on the binary variable, the primary outcome indicator, to secure an appropriate number of participants for stable and sufficient power. The primary endpoint of this clinical trial is
 
                                                                                                                                                                                                                                                                                                                                    |

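### The 15% dropout is taken off the minimum of 396, and the resulting 342 is labelled the number to recruit, which contradicts the plan to enrol 396

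*Protocol*

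**What the plan says.** All statements are in the protocol, in the overview row on the number of study participants and in Section 6 (Sample size calculation).

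- **Minimum.** Both places derive 396 patients, 198 per group, as the minimum for 80% power at the 0.05 level with a within-cluster coefficient of 0.015. "The number of institutions in both groups is three", so this is 66 per hospital.
- **Enrolment, first figure.** The overview says "A total of 396 patients will be enrolled" and gives 66 for the intervention institution.
- **Enrolment, second figure.** After assuming a maximum dropout of 15%, the overview says "the final number of participants to be recruited is approximately 57 for each cluster", 342 in total. Section 6 says "the final number of enrolled study participants should be 57 for each institution, totaling 342 participants".
- **Power.** Section 6 tabulates 0.83007 for 396 patients in 6 clusters at ICC 0.015. Directly after the dropout step, both places add a further figure: "The expected minimum power is 78.8" per cent.
- **Closing statement.** Section 6 ends by returning to 396 expected participants and calling the power sufficient.

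**The concern.** An allowance for dropout is meant to raise the number recruited above the number needed for analysis. Here the number described as recruited or enrolled is lower than the stated minimum, so the label and the arithmetic cannot both be right. The same pages also give 396 as the number to enrol.

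The enrolment target tells each hospital when to stop. A hospital following one sentence stops at 66, and a hospital following the other stops at 57. At the end, nobody can say from the protocol whether 342 enrolled is full recruitment or a shortfall of 54. The stated power is also attached to an ambiguous number: 78.8% describes 342 patients analysed, and it is not the power if 342 are enrolled and some are then lost.

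**Working it through.** **1. Where 342 comes from.** 396 / 6 = 66 per hospital. 66 x 0.85 = 56.1, written as 57. 57 x 6 = 342. This is the number left after 15% loss from 396, with 56.1 rounded up. Without rounding, 396 x 0.85 = 336.6.

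**2. What inflation would give.** 66 / 0.85 = 77.6, so 78 per hospital and 78 x 6 = 468. No figure of this kind appears in the protocol, so nothing in it is inflated for dropout.

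**3. Reproducing the protocol's power.** Inputs from Section 6: "a significance level of 0.05 to control for type 1 error" (taken as two-sided; the sidedness is not stated), three hospitals per group, 1:1 allocation, ICC 0.015, effect size 0.2, logistic GEE analysis. The rates behind the power table are not stated. I assume 50% and 30% because this pair reproduces the printed figures (its mirror, 70% and 50%, gives the same results).

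With m patients per hospital and n = 3m per group:

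- log odds ratio = ln[(0.5/0.5)/(0.3/0.7)] = 0.8473
- variance term V = 1/(0.5 x 0.5) + 1/(0.3 x 0.7) = 8.762
- design effect D = 1 + (m - 1) x ICC
- standard error = sqrt(V x D / n)
- power = Phi(0.8473 / standard error - 1.960)

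For m = 57 and ICC 0.015: n = 171, D = 1.840, standard error = 0.3070, ratio = 2.759, power = 0.788. This is the protocol's 78.8%. The table rows at ICC 0.01 and 0.02 also reproduce to the printed decimals. The rows labelled 0.015 reproduce exactly only at ICC 0.014: 0.83007 for 396, against 0.8176 at 0.015. Both values are therefore shown below.

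**4. Power under each reading.**

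| Scenario | Per hospital analysed | ICC 0.015 | ICC 0.014 |
|---|---|---|---|
| 396 enrolled, none lost | 66 | 81.8% | 83.0% |
| 342 analysed (protocol's post-dropout figure) | 57 | 78.8% | 80.0% |
| 396 enrolled, 15% lost, unrounded | 56.1 | 78.5% | 79.7% |
| 342 enrolled, 15% lost (342 x 0.85 = 290.7) | 48.45 | 75.1% | 76.3% |

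At ICC 0.015, 80% needs 61 analysed per hospital (80.2%; 60 gives 79.9%). The 396 target can therefore absorb 5 losses out of 66 per hospital, about 7.6%, but not 15%.

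**5. Sensitivity to the inferred rates.** At ICC 0.015, 396 less 15% gives 76.9% for 60% vs 40%, and 83.1% for 40% vs 20%. For 342 less 15% the figures are 73.5% and 80.0%. Neither pair reproduces the protocol's 78.8%: at 57 per hospital they give 77.3% and 83.4%.

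**The case against.** The strongest reply is that this is a slip of labelling. The number 342 makes sense as the evaluable number out of 396, and 66 per hospital, 198 per group and 396 expected participants all appear elsewhere. The 78.8% is openly reported as a minimum after dropout. That reading of the numbers is probably what was meant, and the power after dropout is not concealed. But the wrong label stands in two places, and Section 6 uses the word enrolled for 342 just before it returns to 396.

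A second reply is that 15% is an upper bound on loss. Under the overview's suspension criteria and Section 13.C, record review and data linkage continue for many patients who are suspended, and the analysis keeps data up to dropout. The primary endpoint may therefore be known for some patients counted as dropouts. This is fair, but the sample-size section takes no credit for it.

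A third reply is that the 75% scenario counts dropout twice. That is true if 342 is understood as already reduced. It becomes real only if a hospital takes the recruitment sentence literally.

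A reader might infer that neither 396 nor 342 delivers 80% power. The documents do not support that without qualification, because 396 exceeds 80% before dropout, both in the protocol's table and on recomputation.

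**Conclusion.** The contradiction is certain and needs no modelling: 342 is a post-dropout number presented as a recruitment number, and it conflicts with the stated enrolment and minimum of 396. The gap is 54 patients, 9 per hospital.

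The effect on power is modest if 396 is enrolled. The design target of 80% is met before dropout (81.8% to 83.0%). After the maximum 15% loss, power is about 78.5% to 78.8% at the stated ICC of 0.015, or about 80% at 0.014. If 57 per hospital is used as the stopping point and 15% are then lost, it is about 75% (76% at ICC 0.014). These figures rest on the inferred rates of 50% and 30%, a two-sided test, and dropouts contributing nothing to the endpoint.

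A reader might also infer that the trial has to enrol 468, or that the 80% claim should be struck out. Neither follows. The figure of 468 applies only if 396 must remain evaluable, and 80% is a legitimate design target as long as the protocol says it refers to power before dropout.

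**What to change.** In the overview and in Section 6, state one target, for example: *Enrol 396 patients (66 per hospital). With a maximum dropout of 15%, about 336 to 342 (56 to 57 per hospital) are expected to be evaluable, giving a minimum power of about 78.5 to 78.8%.* Remove 342 and 57 wherever they are described as recruited or enrolled. Keep 80% as the design target, and say that at ICC 0.015 it is met before dropout but not after the maximum dropout.

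The cost is wording only. No further patients are needed, and the headline power becomes slightly less favourable. If the sponsor wants 80% after dropout on the same assumptions, 61 evaluable per hospital means 61 / 0.85 = 71.8, so 72 per hospital and 432 enrolled. That is an option, not a condition of the correction.
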